### Ethical issues, including: Ethics committee approval

The study has been approved by the Scotland (A) Research Ethics Committee, reference number 08/MRE00/6.

### Interim analyses and stopping rules

Interim unblinded analyses will be performed on safety, efficacy and possibly futility criteria for the purposes of review by the independent Data Monitoring Committee (iDMC) only. Masking will be maintained and analysis of obstetric and neonatal outcomes will be deferred until conclusion of the two-year childhood assessments. Thus no interim analyses will be revealed to investigators, participants, or anyone other than the DMC members (and statistical advisors) until completion of the two-year childhood assessments.

### Committee oversights

There is an independent Trial Steering Committee and independent Data Monitoring Committee.

### Indemnities

The sponsor has clinical trial insurance which covers this study. This insurance includes indemnification for the TSC and DMC. There is no “no fault” indemnity.

### Publication plan

The results of the trial will be published in peer reviewed journals. The results of the obstetric and neonatal outcomes will not be published until data collection for the childhood follow up part of the study is complete.

### Start date

Recruitment began in January 2009, as of May 2012, over 800 women had been randomized

### End of data collection

Estimated October 2015

### Reporting date

Estimated mid 2016

### Trial registration

ISRCTN14568373

## Discussion

Despite the many publications on the use of progesterone for the prevention of preterm birth, we believe that that further data, particularly on the long term effect for the baby, is needed before the use of progesterone can be routinely recommended in pregnant women at high risk of preterm birth. Many authorities, including the FDA^a^ and the Royal College of Obstetricians in the UK^c^ agree. The Society of Obstetricians and Gynecologists of Canada (SOGC) [25] suggests that women at risk of should be encouraged to enroll in trials of progesterone, although the SOGC also gives advice about the dose and formulation of progestogens for women who have opted to take them. Other authorities endorse the use of progesterone based on current literature. For example the American College of Obstetricians and Gynecologists, in guidelines published in 2008 and reaffirmed in 2011 [26] is more positive about the use of progesterone, saying that “progesterone supplementation for the prevention of recurrent preterm birth should be offered to women with a singleton pregnancy and a prior spontaneous preterm [before 37 weeks] birth” and that “progesterone supplementation for asymptomatic women with a very short cervical length (less than 15 mm) may be considered”. In 2012, the Society of Maternal and Fetal Medicine Publications committee suggests that women with singleton pregnancies with prior preterm birth be given 17 alpha hydroxyprogesterone, and that those with a short cervix ≤ 20 mm be given vaginal progesterone (although they indicate that routine screening is “an object of debate”) [13].

The OPPTIMUM study will provide further evidence on the effectiveness of vaginal progesterone for the prevention of preterm delivery in selected high risk women. Crucially, it will also determine whether prevention of preterm birth by progesterone prophylaxis is associated with long term benefit for the baby.

## Appendix

### Sample size calculations

#### Original sample size calculation based on data in the literature on the “fFN +” group

A sample size of 750 (375 per group) gives adequate statistical power to detect clinically important and plausible differences in the three primary measures of outcome. All these power calculations allow for loss to follow up rates and compliance. Delivery <34 weeks on placebo is expected to be 40% (data from an untreated high risk UK population with a positive fFN test at 22 weeks [27] and 27% on progesterone consistent with the odds ratio of 0.45 for the overall PTB with any progestational agent in the most recent systematic review [28]. With 750 randomised, the study will have 95% power at a 5% level of significance to detect such a reduction from 40% to 27% using a two-sided binomial test. For a more modest reduction from 40% to 30% (odds ratio 0.64) the study would still have 80% power. For the neonatal outcome, the Meis study found 7.2% died, 14.6% had CLD and 5.2% had IVH on placebo, compared to 4.6% death, 8.6% CLD and 1.3% IVH on progesterone [4]. Our neonatal primary outcome is a composite of these and also includes non-haemorrhagic brain injuries. With n = 750 randomised, the OPPTIMUM study would have 80% power at a 5% level of significance to detect a difference in this composite outcome of death, brain damage, or chronic lung disease from 20 to 12%, using a binomial test.

The childhood developmental outcome at 2 years will be assessed using the Bayley III Cognitive Scale which correlates well with later IQ. With 750 randomised, the study will have 93% power at a 5% level of significance to detect a difference in means equivalent to 0.25 of a standard deviations, using a two sample two sided *t*-test. Based on previous work [29], we estimate the standard deviation will be about 15 points, enabling us to detect a difference of 4 points in the Bayley Score. In clinical terms, a difference of 4 points is small, thus the power of the study to detect larger, more clinically significant differences, is high. We have powered this outcome at over 90% to make some allowance for a possible dilution of the power due to incorporating the deaths (using a two stage statistical model).

#### The revised sample size calculation below, based on blinded data (as of April 2011) and inclusion of the "fFN"- group is around 1250 participants

**Obstetric outcome** (delivery <34 weeks).

The table below gives the estimated power for three combinations of sample size (all 1:2 fFN+/fFN- groups, assuming 375:750 (total 1125), 400:800 (total 1200) and 425:850 (total 1275) assuming (fFN+, fFN-) event rates (delivery < 34 weeks) of (40%, 10%), (45%, 13%), and (45%, 15%). All calculations assume a relative treatment effect of 32.5%.

The justification for these combinations is as follows:

1. The 40% untreated rate is as per the original assumption. We have looked at the blinded (aggregated) event rate for the first 67 women randomised in OPPTIMUM (ignoring any possible bias created by recording the early births before later births in the most recently randomised). For the fFN + group, 29/67 (43%, 95% exact confidence interval 31% to 56%) had delivered at <34 weeks. The blinded event rate according to the assumed 40% untreated rate with a 27% treated rate (32.5% relative reduction) would be 33.5%. Although the numbers are relatively small, there appears to be a higher event rate than anticipated, which would be consistent with having selected a higher risk and hence scarcer subset than we planned for). An overall blinded rate of 43% could comprise an untreated rate of 52% and a treated rate of 35%. We assume conservatively that the baseline event rate in the untreated fFN + group is 45%.

2. For the fFN- group women data on the first 24 women suggested that 8/24 (33%, exact 95% confidence interval 16% to 55%) had delivered early. As indicated above, this percentage is likely to be inflated since we record the early deliveries before observing the term deliveries. However, fortunately, we also had followed up those who were not randomised (by definition, all of whom had a negative fFN test) into OPPTIMUM from the start. Of the 398 followed, 32 have had a delivery <34 weeks. We know that 57% of these 398 would have been eligible for the trial (short cervix < 25 mm), and the epidemiology indicates that it is very unlikely to give birth <34 weeks with none of the classic risk factors. So we conservatively estimate that around 13% (i.e. around 29/225, exact confidence interval 9% to 18%) of those recruited into the fFN- group, based on OPPTIMUM data, will have a delivery <34 weeks.

The conclusion is that it seems likely that if we recruit at least 1125 (375:750) we will have almost 90% for the primary obstetric outcome, assuming a slightly higher rate in the fFN + group (45% rather than 40%) and a corresponding untreated event rate of 13% in the fFN- women. If as we expect from the early returns the fFN- event rate is >15%, we will be comfortably powered at the original 95% for the obstetric outcome. Table 1 shows the various power scenarios.

**Table 1 T1:** Power scenarios for the neonatal outcome

**fFN+**	**fFN-**	**Subjects (fFN+/fFN-) [Total]**	**Power**
40%	10%	375/750 (1125)	81%
		400/800 (1200)	83%
		425/850 (1275)	85%
45%	13%	375/750 (1125)	88%
		400/800 (1200)	90%
		425/850 (1275)	92%
50%	15%	375/750 (1125)	93%
		400/800 (1200)	94%
		425/850 (1275)	95%

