### Statistical analysis plan, including sample size and power calculations

At the commencement of the study in 2008, we planned to recruit 750 women in the “fFN positive” group. We estimated that such a sample size would provide 80 – 95% power at the 5% level of significance for the primary obstetric outcome, 80% power for the neonatal outcome and 93% power for the childhood outcome (although further dilution of the latter was anticipated after incorporation of the deaths in a two stage statistical model – see below).

In 2010, the study was expanded to allow randomisation of women in the “fFN negative” group after analysis of preliminary (blinded) data in July 2010, together with the result of an HTA funded systematic review on screening for preterm birth [23] showed that our initial selection strategy erroneously missed women at medium to high risk of preterm birth. This change was endorsed by the Trial Steering committee, the MHRA, the ethics committee, and by the funder. The inclusion of women at a lower risk of the primary outcomes necessitated an increase in the sample size. The minimum new sample size is anticipated to be in the order of 1125 (375 fFN positive and 750 fFN negative women), but the proportions of each will dictate the exact sample size, as it is anticipated that at least 2 fFN negative women are required to achieve the event rate predicted in 1 fFN positive woman. Workings for the sample size calculation for the fFN positive group alone, and for the revised combined group of fFN positive and fFN negative women are shown in the Appendix.

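### The 95% obstetric power claim rests on a 50%/15% scenario that the text gives as 45%/15%; at 45%/15% power is about 91% to 94%, and the 13% fFN-negative rate is not conservative for its cohort

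*Protocol article*

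**What the plan says.** All statements are in the protocol article's appendix, in the revised sample size calculation.

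- **Scenarios.** The obstetric paragraph announces "event rates (delivery < 34 weeks) of (40%, 10%), (45%, 13%), and (45%, 15" per cent as the last pair, for 375:750, 400:800 and 425:850 fFN-positive to fFN-negative women. It adds: "All calculations assume a relative treatment effect of 32.5" per cent.
- **Table 1.** The caption names the neonatal outcome, but the rates and powers are the obstetric ones. The third block is 50%/15%, with 93%, 94% and 95% power at 1125, 1200 and 1275.
- **fFN-positive rate.** Item 1 adopts 45% for untreated women and calls this conservative.
- **fFN-negative rate.** Item 2 reports early delivery in 8 of 24 randomised women (33%) and says this is probably inflated, because early births are recorded before term births. It turns to women followed but not randomised: "Of the 398 followed, 32 have had a delivery <34 weeks", of whom 57% would have been eligible. From these: "So we conservatively estimate that around 13" per cent, given as 29/225 with an interval of 9% to 18%.
- **Conclusion.** At least 1125 women give almost 90% power at 45%/13%. Then: "If as we expect from the early returns the fFN- event rate is >15%, we will be comfortably powered at the original 95" per cent.

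**The concern.** The third scenario differs between text and table, and the difference favours the design. The only 95% in Table 1 sits in that block, at 1275 women. The text adopts 45% for fFN-positive women and never announces 50% as a scenario, so the 95% assurance depends on a rate that the text does not adopt.

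The condition attached to the assurance is also weakly supported. The text discounts the early returns and moves to the cohort, then returns to the early returns for its expectation of more than 15%. The 13% from the cohort is called conservative although it assigns nearly all early births to the eligible women.

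At stake is how much power a reader attributes to a trial that stops at its stated minimum of 1125.

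**Working it through.** **Inputs.** Relative reduction 32.5%, so treated rate = 0.675 × untreated rate. This agrees with the original calculation (27/40 = 0.675), which was made "to detect such a reduction from 40% to 27% using a two-sided binomial test". Two-sided 5% and equal arms are carried over from that calculation; this is an assumption, supported by the match below. fFN-positive to fFN-negative ratio 1:2.

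**Formula.** With fFN-positive rate a, fFN-negative rate b and total N:

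- p = a/3 + 2b/3; q = 0.675p; n = N/2; p̄ = (p + q)/2
- d = p − q − 1/n (continuity-corrected)
- power = Φ{[d − 1.96·√(2p̄(1 − p̄)/n)] / √([p(1 − p) + q(1 − q)]/n)}

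**Step 1: reproduce Table 1, then run the announced pair.** Powers in % at 1125/1200/1275:

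| fFN+/fFN− | p | Printed | Corrected | Uncorrected |
|---|---|---|---|---|
| 40/10 | 0.2000 | 81/83/85 | 81.1/83.7/85.9 | 83.2/85.5/87.5 |
| 45/13 | 0.2367 | 88/90/92 | 88.6/90.6/92.2 | 90.0/91.8/93.2 |
| 50/15 | 0.2667 | 93/94/95 | 92.9/94.3/95.5 | 93.8/95.1/96.1 |
| 45/15 | 0.2500 | none | 90.7/92.4/93.9 | 91.9/93.4/94.7 |

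The corrected form matches all nine printed cells within about one point, so the printed third block was computed at 50%/15%.

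Worked line for 45/15 at 1125: n = 562.5, q = 0.16875, d = 0.08125 − 0.00178 = 0.07947, p̄ = 0.20938. The null term is 1.96 × 0.02426 = 0.04755 and the denominator is 0.02414. Then (0.07947 − 0.04755)/0.02414 = 1.322, and Φ = 0.907.

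**Step 2: fFN-negative rate needed for 95%.** Corrected method, with the uncorrected value in brackets:

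| N | fFN+ 45% | fFN+ 50% |
|---|---|---|
| 1125 | 20.7% (19.4%) | 18.2% (16.9%) |
| 1200 | 18.6% (17.4%) | 16.1% (14.9%) |
| 1275 | 16.7% (15.6%) | 14.2% (13.1%) |

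**Step 3: what the cohort gives.** 0.57 × 398 = 227 eligible women, leaving 171.

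- All 32 events in eligible women: 32/227 = 14.1%.
- The plan's split: 29/225 = 12.9%, leaving 3/171 = 1.8% in the others. So 29/32 = 91% of events fall in 57% of the women.
- Events spread evenly: 32/398 = 8.0%.

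**Step 4: power at 1125 with fFN-positive 45% (corrected).**

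| fFN− rate | Power |
|---|---|
| 8% | 82% |
| 10% | 85% |
| 13% | 89% |
| 14.1% | 90% |
| 15% | 91% |

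**The case against.** **The 95% sentence names no sample size.** This stands. The section heading says around 1250, and at 50%/15% the table's method gives 95.2% at about that size. The preceding sentence speaks of 1125, so the wording is ambiguous. Naming 1250 does not help at the adopted 45%, where 15% gives less than 95% even at 1275.

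**The condition is open-ended.** Also true: a high enough rate above 15% gives 95%. At 1125 with fFN-positive 45%, that rate is about 21%.

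**The planned test has no continuity correction.** The obstetric analysis is a likelihood ratio test, so the uncorrected column may be nearer. It brings 45%/13% at 1125 to 90.0%, and almost 90% stands. For 45%/15% it still gives only 91.9% to 94.7%.

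**Stratifying by fFN status would gain power.** A Mantel-Haenszel type calculation gives about 94% at 1125 and 95% at 1200 for 45%/15%. However, it does not match Table 1, and the stated obstetric model contains only treatment and previous pregnancy.

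**Stronger readings that a reader might infer.** The documents do not support these:

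- *That the data rule out a rate above 15%.* The 14.1% caps only the cohort's point estimate. The printed interval reaches 18%. The early returns, though biased, have a lower limit of 16% and, being blinded, may include treated women.
- *That 8% is the neutral estimate.* It assumes no excess risk in eligible women, and the plan argues the opposite. It is a lower bound for display.
- *That low power was hidden.* Table 1 already prints 81% for 40%/10% at 1125.
- *That fFN-negative women may replace fFN-positive women two for one.* The phrase "at least 2 fFN negative women are required to achieve the event rate predicted in 1 fFN positive woman" sets a floor, which ratios of 3.5 (45/13) or 4 (40/10) satisfy. The neonatal paragraph also asks for at least 375 fFN-positive women.
- *That the oversight bodies relied on the 95% figure.* The recorded endorsement concerns the 2010 expansion of eligibility, whereas this calculation uses April 2011 data.

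**Conclusion.** The point holds as a wrong power statement and an internal contradiction. It does not show an underpowered trial.

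- Text and Table 1 disagree on the third scenario, and the printed powers belong to the pair that the text does not announce.
- At the adopted fFN-positive rate of 45%, an fFN-negative rate of 15% yields about 4 points less than the claimed 95% at 1125, and about 1 point less at 1275.
- The word conservatively is justified for the 13% only against the discounted 33%. Against the cohort it came from, 13% lies about one point below the highest possible point estimate.

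The practical effect is moderate: with fFN-positive at 45%, power at 1125 stays above 80% even at the 8% lower bound. These figures assume equal arms, a 1:2 fFN mix, a 32.5% relative reduction in both groups, and an unstratified two-sided 5% comparison.

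**What to change.** 1. Reconcile the third scenario between the obstetric paragraph and Table 1. If 50%/15% is kept, announce and justify it; if 45%/15% is meant, print about 91%, 92% and 94%.
2. Replace the 95% sentence with the power at fFN-positive 45% and a named sample size: about 91% at 1125 and 94% at 1275 for 45%/15%.
3. Drop the word conservatively for the 13%, and say that it assigns 29 of the 32 early births to the eligible women.
4. Add power at 1125 with fFN-positive 45% for lower fFN-negative rates: about 82% at 8%, 85% at 10%, 89% at 13% and 90% at 14%.

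The cost is appendix wording and a few table rows. The stated power becomes less favourable. Sample size, design and analysis do not change.

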**The neonatal outcome** (neonatal death, severe chronic lung disease, intraventricular haemorrhage)**.**

Data from the first cohort of women randomised (and in particular those randomised in the low risk group) into OPPTIMUM was even sparser for this outcome, as it is determined by convention to up to 30 days after a full term birth. For all those randomised with mature data at the time of analysis, 11/68 have had the composite neonatal outcome (16%, exact 95% confidence interval of 8% to 27%). Given that the rate of pre-term birth is higher than anticipated, it seems reasonable to inflate the assumed neonatal event rate from 20% to 25% (giving an blinded event rate of 20%, assuming a 40% relative reduction – and 20% is very consistent with the observed 95% confidence interval of 8% to 27%). If we then further assume a pro-rata event rate in line with the rates of delivery <34 weeks on the obstetric outcome, with the fFN- having roughly one-third the events of the fFN + i.e. 8% rather than 25%, then Table 2 below shows the various power scenarios:

**Table 2 T2:** Power scenarios for the obstetric outcome

**fFN+**	**fFN-**	**Subjects (fFN+/ fFN-) [Total]**	**Power**
25%	8%	375/750 (1125)	81%
		400/800 (1200)	83%
		425/850 (1275)	86%

We conclude that by randomising at least 375 fFN + and 750 fFN- women, assuming an untreated rate of 25% of the composite of neonatal death, severe chronic lung disease, intraventricular haemorrhage in the fFN+, and 8% in the fFN-, with an assumed 40% relative treatment effect (as per original calculation) the original power of the study for this neonatal outcome will be preserved at >80% power.

**The childhood development outcome** (Bayley Score at 2 years).

There are no data yet on this outcome within OPPTIMUM. In the original calculation we assumed that the difference in mean Bayley score would be 4 units with a common standard deviation of 15 units. It is more difficult to assess the power convincingly with a mixture of fFN + and fFN- women on a continuous outcome such as the Bayley Score, since the power calculation requires assumptions about not just the anticipated treatment effect but also the assumed variability via the standard deviation. If we assume the same 4 unit difference in the fFN + and a 4/3 unit difference in the fFN- group (consistent with the pro-rata rate of delivery <34 weeks), with the same 15 unit standard deviation, then the study will have 71%, 73%, and 76% power if 1125, 1200, or 1275 are randomised (375:750, 400:800; and 425:850) as per Tables 1 and 2 above. However, this is for an unadjusted analysis, and in practice we will adjust for fFN + and fFN- group, and a limited number of other baseline covariates strongly related to Bayley Score at 2 years (e.g. gender) as specified in the statistical analysis plan, and this will reduce the variability and hence increase the power. For example, if the underlying variability in the lower risk group is lower – say halved, at 7.5 units, consistent with a higher proportion having uniformly high Bayley Scores since they have no disability – then the approximate power would be 93%, 94%, and 95% respectively for 1125, 1200, or 1275 randomised in total. In practice the reduction in variability by adjusting for both this design variate (fFN + and fFN- ) and additional baseline covariates may be considerably greater, so we are confident that the original power on the childhood development outcome will be protected at or above the original 90% level by randomising at least 1125 subjects (375:750).

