## Background, including rationale and any previous systematic review(s)

Preterm birth is a global problem, with a prevalence of 8 to 12% depending on location [1]. Around 75% of preterm birth follows spontaneous preterm labour, sometimes preceded by preterm premature membrane rupture [2]. Babies born preterm are at increased risk of a variety of adverse short term (neonatal) and long term complications, including neurodevelopmental disability. Women with a previous preterm birth (especially those women who delivered before 34 weeks following spontaneous preterm labour), women with a short cervix in early pregnancy [3], and women with a previous cone biopsy or laser loop excision to the cervix [4] are at all at increased risk of spontaneous preterm birth.

Several large trials and meta-analyses have shown progesterone to be effective in preventing or delaying preterm birth in selected high risk women (short cervix or previous preterm birth) with singleton pregnancy [5-11]. There is data that both intramuscular 17 hydroxyprogesterone caproate and vaginal progesterone are effective in preventing preterm birth. OPPTIMUM likewise is investigating the efficacy of progesterone in women at elevated risk of preterm birth, but will crucially address longer term childhood developmental outcomes.

Although an improvement in short term neonatal outcomes has been shown in some trials [6-8] these have not consistently been confirmed in meta-analyses [9,10]. Data on longer term outcomes in singletons is limited to follow up of babies of women in the Meis trial, where 80% of babies were assessed by questionnaire at a mean age of four years. No differences in childhood outcomes were demonstrated, despite the progesterone group having a lower incidence of preterm birth [12].

The mechanisms of action of progesterone are somewhat uncertain although a direct inhibitory effect on the processes of parturition seem likely [13]. Additionally progesterone could exert anti-inflammatory properties [13] and/or direct CNS protective effects [14], which could help to reduce the risk or severity of long term neonatal problems.

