#### Childhood outcome

The primary childhood outcome is the Bayley III score, a continuous measure. This outcome will, by definition, not be available on babies who have died. Thus deaths need to be incorporated into the analysis, since the number of deaths may be sufficiently large as not to be negligible, and/or there may be a difference in the number of deaths between the two randomised groups. We will therefore use a two-stage statistical model that jointly models the treatment effect in both deaths and survivors [24], with deaths modelled using a binomial test and survivors modelled using a generalised linear model. The two parts are then combined to form the appropriate test statistic. Secondary analyses that adjust the estimated treatment effect for covariates felt to be of importance will be used as appropriate. Note that we will not be adjusting for gestational age in our analysis of childhood outcomes. The hypothesised mechanism of action of progesterone is to increase gestational age by reducing the proportion of women giving birth prematurely. To adjust for a post randomisation covariate (gestational age) which is a direct measure of the treatment effect, in a model that is estimating the consequence of that treatment effect (in terms of developmental outcome) is not statistically sound.

A fully detailed Statistical Analysis Plan will be prepared prior to unblinding.

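### The conclusion that childhood power stays at or above 90% with 1125 women is not supported by the appendix's own arguments: it rests on an assumed halving of one standard deviation, not on covariate adjustment

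*Protocol article*

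**What the plan says.** All places are in the protocol article.

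- **Appendix, original sample size calculation.** With 750 women, "the study will have 93% power at a 5% level of significance to detect a difference in means equivalent to 0.25 of a standard deviations", for a two-sided two-sample t-test. The SD is put at about 15 points, and the detectable difference is given as 4 points. The section states: "All these power calculations allow for loss to follow up rates and compliance". It gives no loss rate. It says that powering above 90% leaves some room for dilution from bringing deaths into the analysis.
- **Appendix, revised calculation, childhood development outcome.** Assuming 4 points in fFN-positive women, 4/3 points in fFN-negative women and SD 15, "then the study will have 71%, 73%, and 76% power if 1125, 1200, or 1275 are randomised". The text then says that the analysis will adjust for fFN group and a few baseline covariates, naming gender, and that this will raise power. Its numerical example halves the fFN-negative SD to 7.5 and gives 93%, 94% and 95%. It adds that the true reduction in variability may be larger still, and concludes that "we are confident that the original power on the childhood development outcome will be protected at or above the original 90% level" with at least 1125 women. The paragraph opens by acknowledging that the trial has no data on this outcome.
- **Methods, Childhood outcome.** The primary analysis is a two-stage model, with a binomial part for deaths and a generalised linear model for survivors. On adjustment: "Secondary analyses that adjust the estimated treatment effect for covariates felt to be of importance will be used as appropriate".

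**The concern.** The step from 71% to 90% is credited to covariate adjustment, but the only number behind it is a different assumption about raw variability. The Methods do not clearly place the adjustment in the primary test. Loss to follow-up and deaths, both mentioned in the original calculation, do not appear in the revised figures.

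Childhood development at two years is one of three primary outcomes, and the Background presents it as the question that earlier trials left open. A null result would be read against the claim of at least 90% power. If the SD is 15 in both strata, the same appendix supports only about 70%.

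**Working it through.** **Inputs.** From the Appendix: two-sided 5% test, equal arms, effects 4 and 4/3 points, fFN-positive to fFN-negative ratio 1:2, SD 15 (or 7.5 in fFN-negative women in the example), total 1125, 1200 or 1275. Assumed here: loss rates, R² values and intermediate SDs.

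**Formula.** Power ≈ Φ(δ / (σ√(2/n)) − 1.96), with n per arm. A noncentral t gives the same results to within 0.1 percentage point.

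**1. Original figure.** δ/σ = 0.25 and n = 375: 0.25/√(2/375) = 3.42, power 92.8% (stated 93%). This uses every randomised child. With an assumed 20% loss (n = 300) it is 86.5%.

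**2. Revised base case.** δ = (4 + 2 × 4/3)/3 = 2.222. At 1125, n = 562.5 and 2.222/(15√(2/562.5)) = 2.485.

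| Total | Stated | Recomputed |
|---|---|---|
| 1125 | 71% | 70.0% |
| 1200 | 73% | 72.8% |
| 1275 | 76% | 75.3% |

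These also use every randomised woman.

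**3. Halved-SD example.** Pooled within-stratum SD = √((15² + 2 × 7.5²)/3) = 10.61. With no covariate in the model, power is 94.0%, 95.2% and 96.3% (stated 93%, 94%, 95%). The stated figures are therefore reached by changing the raw SD alone. Adjusting for fFN status in this example still gives 94% at 1125.

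**4. Sensitivity to the fFN-negative SD, at 1125.**

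| fFN-negative SD | Power |
|---|---|
| 7.5 | 94% |
| 9 | 91% |
| 10 | 88% |
| 12 | 81% |
| 13.5 | 76% |
| 15 | 70% |

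**5. What adjustment would have to deliver at SD 15.** 90% power needs a residual SD of 2.222/((1.960 + 1.282)√(2/562.5)) = 11.50, so R² = 1 − (11.50/15)² = 0.41. With residual SD = 15√(1 − R²), an R² of 10%, 20% or 30% gives 75%, 79% or 84%.

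fFN status alone, at a 1:2 split, explains (2/9)D²/225, where D is the difference in mean score between strata. R² = 0.41 would need D of about 20 points. The appendix's pro-rata logic implies much less. It ties 4 points to 45% × 32.5% = 14.6 percentage points of early delivery, and the strata differ by 45 − 13 = 32 percentage points, so D ≈ 4 × 32/14.6 ≈ 8.75. That gives R² = 7.6% and power 73%. If 15 is already the within-stratum SD, adjusting for fFN status adds nothing.

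**6. Loss to follow-up (assumed 20%), at 1125.** n = 450 per arm gives 60% at SD 15 in both strata and 88% in the halved-SD example.

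**The case against.** **The arithmetic is sound.** Both sets of figures reproduce within 2 percentage points. The appendix prints the 71–76%, concedes that power is hard to assess for this outcome, and makes the 93–95% conditional. That stands: nothing is miscalculated, and the fault lies in the inference drawn.

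**A reader might infer that adjustment cannot close the gap.** That goes too far. An R² of about 0.41 would do it, and the document gives no R². The supportable statement is that the gap has not been shown to close.

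**A reader might infer that true power is 50–70%.** The documents do not support that range.
- No loss rate is stated for this trial. The 20% above matches the Background's account of an earlier trial, in which "80% of babies were assessed by questionnaire at a mean age of four years". That was a different assessment at a different age.
- The 50% end also needs a 2-df combined test with no difference in deaths. The Methods do not fix the form of the combination. At 1125 and SD 15, a 2-df test (noncentrality 2.485² = 6.17) gives 60% with no death difference, or 50% with 20% loss.
- The original calculation cites deaths of 7.2% versus 4.6%. Scaling these by one third in fFN-negative women (an assumption) gives (7.2 + 2 × 2.4)/3 = 4.0% versus (4.6 + 2 × 1.53)/3 = 2.56%. Power is then about 72%, or 64% with 20% loss of Bayley scores. The two-part test may therefore lower or raise power.
- The range leaves out a smaller fFN-negative SD altogether.

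**Adjustment may be fixed in the analysis plan.** The Appendix refers to that plan for the covariates, and the Methods do not list the terms of the survivor model. So it is not established that the primary test lacks the adjustment. The two sections still need to agree.

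**The loss sentence is not wrong throughout.** For the neonatal outcome, 20% versus 12% with 375 per arm gives about 85% against a stated 80%, which leaves room for loss. On the childhood side, an exact 4 points on SD 15 is 0.267 SD and gives 95.5% with no loss. The 93%, however, is tied to 0.25 SD, where no room remains.

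**Conclusion.** The point holds as one of unsupported inference. On the appendix's stated effects, power at 1125 is about 70% if the SD is 15 in both strata. It reaches 93–94% only if the fFN-negative SD is 7.5, and for that the trial had no data. Adjustment for fFN status and gender is not shown to supply the difference: 90% at SD 15 needs an R² of about 0.41. The claim of protection at or above 90% therefore depends on an unverified SD and should not be unconditional.

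For the childhood outcome, the original 93% at 0.25 SD carries no allowance for loss, contrary to the section's general statement. The revised figures carry neither loss nor the dilution from deaths that the original section mentions.

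The roughly 70% needs only the appendix's own inputs. The loss results rest on a rate assumed here, and the results for the two-part test also on an assumed form of that test. Power is uncertain between these scenarios; it is not known to be any single low figure.

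**What to change.** 1. Withdraw the unconditional conclusion. State childhood power at 1125 as about 70% with SD 15 in both strata, 81% with fFN-negative SD 12, 88% with SD 10, and about 93–94% only with SD 7.5. Alternatively, justify a particular SD or R² and show the range around it.
2. Add a loss scenario labelled as an assumption, for example 20% loss: about 60% at SD 15 and 88% at fFN-negative SD 7.5. Note that the two-part test may move these figures either way, depending on the difference in deaths.
3. Correct the original section's sentence on loss to follow-up for the childhood outcome.
4. Reconcile the Methods with the Appendix. Either prespecify fFN status and the named baseline covariates in the primary survivor model, or stop crediting adjustment in the power statement.

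The cost is wording in the Appendix and Methods, matched in the analysis plan. No extra women are needed, but the stated power becomes less favourable.
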